### Outcomes

The primary endpoint of this study is the average service life of the CRRT circuit or filter. The functional lifespan of CRRT circuit begins when the extracorporeal circulation of blood starts and ends when the circuit is taken out of service by intensive care unit (ICU) staff (when the treatment goal is achieved, death occurs, or the upper limit of 72 h for filters). The reasons for ICU staff to stop the circuit operation included: (1) the transmembrane pressure on both sides of the circuit exceeded 300 mmHg, (2) visible blood clots hindered the blood flow within the machine, (3) the blood pump could not rotate due to blood clot blockage, (4) other (recorded by the bedside staff). The first three reasons are considered to be cases of circuit clotting. If the bedside staff recorded “other” or the reason for stopping the circuit was missing, adjudication is required. Two senior critical care specialists, who were not involved in the research, independently reviewed these cases and adjudicated the reasons for circuit discontinuation. In case of any disagreement, they resolved it through joint consultation. The outcome of the judgment may be one of three types (coagulated, non-coagulated or unknown condition). The circuit that is selectively discontinued due to reasons during the treatment process (such as transfer within the hospital) is regarded as “non-coagulated.”

The secondary endpoints of this study include: 1. SOFA and APACHE II scores were evaluated on days 1, 3, 5, and 7 after enrollment, and the changes from the baseline (ΔSOFA /ΔAPACHE II) were calculated to reflect the trend of disease progression; 2. Serum levels of pancreatic enzymes (amylase and lipase) and PCT, CRP, IL-6, IL-8, IL-10 and TNF-α were measured on days 1, 3, 5, and 7, and their changes from baseline were analyzed; 3. levels of coagulation parameters(include aPTT, PT, fibrinogen, platelet count) were assessed on specific days (day 1, 3, 5, and 7) together with their changes from baseline values; 4. time to successful initiation of enteral nutrition; 5. blood transfusion requirements(RBC, FFP, platelet units), 6. ICU length of stay and total hospitalization days; 7. Clinical outcomes (blood purification dependency rate, length of ventilator use and all-cause mortality at 28 days).

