### Sample size estimation

The sample size was estimated based on the primary endpoint, which was average service life of the CRRT circuit lifespan or filter (hours). The assumed baseline value of approximately 30 h for the heparin group, together with the standard deviation used in this calculation, were derived from the pooled filter-lifespan data summarized in the network meta-analysis of CRRT anticoagulation strategies by Zhou et al. and the review of circuit-survival determinants by Tsujimoto and Fujii, which indicate that heparin-anticoagulated circuits typically survive on the order of 20–40 h with considerable between-study variability (17, 32). Because the standard deviation of filter lifespan varies significantly across studies, we deliberately chose a relatively conservative value (σ = 8 h) toward the higher end of the reported range, to avoid underestimating the required sample size. A minimum clinically important difference of 4 h (an approximately 13% relative extension over the assumed heparin baseline) was prespecified not purely on statistical grounds but because a gain of this magnitude would be expected to translate into approximately one fewer circuit change per patient over a typical treatment course, with corresponding reductions in nursing workload and blood loss associated with circuit priming and disconnection, as well as lower filter and consumable costs—benefits that are clinically and economically meaningful even though the absolute increase in hours is modest. Assuming a two-sided α level of 0.05 and a power (1–β) of 80%, the sample size was estimated using the approximate formula for comparing the means of two independent samples, resulting in a sample size of approximately 63 cases in each group. Taking into account the approximately 10% dropout rate, it is necessary to recruit 70 participants in each group.

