### Statistical methods

#### Statistical methods for primary and secondary outcomes

Continuous variables were tested for normality using the Kolmogorov–Smirnov test. Normally distributed data were presented as mean ± standard deviation (SD) and compared using the independent-samples *t*-test. Non-normally distributed variables were reported as median (interquartile range, IQR) and analyzed using the Mann–Whitney U test. Categorical variables were expressed as counts (percentages) and compared using the χ^2^ test or Fisher’s exact test, as appropriate.

In addition, the primary endpoint of this study was the mean lifespan of the hemodialysis filter during CRRT. Kaplan–Meier survival analysis was conducted to compare the cumulative probability of filter life over time, with the log-rank test applied for group comparison. To control for potential confounders (e.g., disease severity scores), multivariable linear regression and Cox proportional hazards models were used as sensitivity analyses.

Secondary outcomes included the changes in disease severity scores (SOFA and APACHE II), pancreatic enzymes (amylase, lipase) and inflammatory biomarkers (PCT, CRP, IL-6, IL-10, TNF-α) measured on Day 1 (baseline), day 3, day 5, and day 7 after randomization. To evaluate time-dependent trends and group differences, a repeated-measures analysis of variance (RM-ANOVA) was applied for normally distributed variables. Baseline disease severity characteristics, including etiology, CTSI/EPIC radiological scores, and the presence and grade of intra-abdominal hypertension, will be summarized descriptively and compared between groups using the χ^2^ test, Fisher’s exact test, or the Mann–Whitney U test, as appropriate. The assumption of sphericity was tested by Mauchly’s test, and when violated, the Greenhouse–Geisser correction was used to adjust degrees of freedom. Differences in change-from-baseline values (ΔSOFA, ΔAPACHE II, and Δbiomarker levels) between groups were analyzed using the independent-samples *t*-test or Mann–Whitney U test, as appropriate. Correlations between the changes in inflammatory markers and changes in severity scores were assessed using Spearman’s rank correlation coefficient.

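### The protocol expects several filters per patient but fixes neither the unit of analysis nor a within-patient method for the log-rank and Cox comparisons of filter life; pooling filters as independent records would push type I error above 5%

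*Protocol article*

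**What the plan says.** The Outcomes section states: "The primary endpoint of this study is the average service life of the CRRT circuit or filter". It then defines the start, the stop and the reason for stopping circuit by circuit. Each circuit stopped for an unlisted or unrecorded reason is adjudicated as coagulated, non-coagulated or unknown. The section does not say whether the average is taken within each patient or over all filters in an arm.

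The Sample size estimation section works in patients. It applies a two-sample formula for means and reports the outcome of that calculation this way: "resulting in a sample size of approximately 63 cases in each group". After dropout it arrives at 70 participants per group. It justifies the 4 h difference partly by a saving of roughly one circuit for each patient over the course of CRRT.

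The section on statistical methods for primary and secondary outcomes gives a t-test or Mann–Whitney test for continuous variables. For filter life it adds: "Kaplan–Meier survival analysis was conducted to compare the cumulative probability of filter life over time, with the log-rank test applied for group comparison". Linear and Cox regression are listed as sensitivity analyses. Mixed-effects models appear only in the section on non-adherence and missing data, as a way to handle missing values.

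**The concern.** Three parts of the plan imply different units. The endpoint is an average, the sample size is one value per patient, and the survival comparison needs a duration and an event status for each record. The Outcomes section supplies an event status per circuit, and a per-patient average has none. With no rule restricting the analysis to the first filter, the most natural reading of the Kaplan–Meier analysis is one record per circuit.

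The ordinary log-rank test and Cox model assume that records are independent. Filters used in one patient share the catheter, platelet count, inflammatory state and bedside staff, so their lives are likely to be positively correlated. Patients who clot often also contribute the most filters. If this is ignored, standard errors are too small, confidence intervals too narrow and p-values too low, and chance differences between patients can be read as a difference between anticoagulants.

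**Working it through.** **1. The plan's own sample size.** Inputs from the Sample size estimation section: difference 4 h, SD 8 h, two-sided α 0.05, power 80%.

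n per arm = 2 × (1.960 + 0.842)² × 8² / 4² = 62.8, so 63. Allowing for 10% dropout, 63 / 0.90 = 70.

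Both stated figures reproduce, and power at 63 per arm is 0.801. They are valid for one independent value per patient.

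**2. Does the plan expect several filters per patient?** It assumes a mean of about 30 h on heparin, hence 34 h on nafamostat. Over T hours of CRRT, the number of filters saved is T/30 − T/34. Setting this to 1 gives T = 30 × 34 / 4 = 255 h (10.6 days), or 255/30 = 8.5 filters against 255/34 = 7.5. Over 5 days (120 h) the figures are 4.0 and 3.5. Several filters per patient is therefore the plan's own premise, although it states no number.

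**3. Type I error if all filters are pooled as independent.** The documents give neither m nor ICC, so both are assumed. With design effect DE = 1 + (m − 1) × ICC, the actual two-sided error of a nominal 5% test is 2 × [1 − Φ(1.96 / √DE)].

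Example: m = 5 and ICC 0.1 give DE = 1.4, and 1.96 / √1.4 = 1.657, so the actual error is 9.8%.

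| Filters per patient (m) | ICC 0.05 | ICC 0.1 | ICC 0.3 |
|---|---|---|---|
| 1 | 5.0% | 5.0% | 5.0% |
| 2 | 5.6% | 6.2% | 8.6% |
| 3 | 6.2% | 7.4% | 12.1% |
| 5 | 7.4% | 9.8% | 18.6% |
| 8 | 9.2% | 13.3% | 26.6% |

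**4. Check on the log-rank test itself.** The formula above is an approximation for a log-rank test, so a naive log-rank test was simulated with no treatment difference. The set-up was 70 patients per arm, m filters each, Weibull filter lives, a shared gamma patient effect, a 72 h cap plus random censoring, and 2,000 trials per setting.

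| Variance of patient effect | m = 1 | m = 2 | m = 3 | m = 5 |
|---|---|---|---|---|
| 0 | 5.1% | 4.7% | 5.2% | 5.2% |
| 0.25 | 4.5% | 6.7% | 8.5% | 11.9% |
| 0.5 | 4.5% | 7.4% | 10.9% | 17.8% |
| 1.0 | 6.0% | 9.3% | 14.3% | 22.1% |

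The patient-effect variance is not an ICC, so the two tables do not match cell by cell. They agree in direction and order of size. The Monte Carlo standard error at 5% is √(0.05 × 0.95 / 2000) = 0.5 percentage points.

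**5. One value per patient.** A further null simulation used 63 per arm, a mean CRRT course of 120 h or 60 h, a lognormal patient effect and 800 trials per setting. At 120 h the pooled log-rank test rejected in 4.9%, 12.5% and 22.9% of trials for a patient log-SD of 0, 0.3 and 0.5. At 60 h (about 3 filters each) it rejected in 9.9% and 14.5% for log-SD 0.3 and 0.5. A first-filter log-rank test and a t-test on per-patient means stayed at about 4–6% throughout.

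**The case against.** The strongest reply is that the protocol never says that all filters enter the log-rank or Cox analysis, or that they are treated as independent. Where it signals a unit, it points to the patient: an average as the endpoint, and a sample size for two independent means counted in participants. A log-rank test on the first filter, or a t-test on per-patient means, would be valid. Cox is only a sensitivity analysis, and nothing clearly ranks the log-rank test above the t-test or Mann–Whitney test. All of this stands. A reader might infer that the plan commits to an invalid primary test, but the documents do not go that far.

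A reader might also infer that type I error will be far above 5%. That depends on m and ICC, which the documents do not give. With two filters and weak correlation, the excess is under one percentage point.

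It can also be said that variance estimators belong in an SAP. That stands for the choice of estimator, but it does not dispose of the point. The article names the tests for the primary endpoint, and for repeated biomarker measurements it specifies a within-patient method with a sphericity correction. For filters, which are also repeated within patients, it names tests that assume independence and says nothing about the unit. The mixed-effects models for missing data do not address this.

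**Conclusion.** The point holds in conditional form. The plan expects several filters per patient, records outcome per circuit, and compares filter life with tests that assume independent records, while leaving open both the unit of analysis and which test is primary. Followed on its most natural reading, it pools correlated filters.

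If it does so, the actual type I error lies between about 5.6% (m = 2, ICC 0.05) and about 27% (m = 8, ICC 0.3), with 9.8% and 18.6% at m = 5 and ICC 0.1 and 0.3. These figures rest on assumed m and ICC and on positive within-patient correlation; with no correlation the error stays at 5%. The documents do not establish that filters will be treated as independent, nor that the inflation will be large. The stated 63 and 70 per arm are not in error for an analysis with one value per patient.

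**What to change.** In the section on statistical methods for primary and secondary outcomes, state that the patient is the unit of inference and name one primary test. Then choose one of:

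- **All circuits:** apply a patient-clustered robust variance, or a shared frailty term, to both the log-rank and the Cox analyses.
- **One record per patient:** restrict the survival analysis to the first filter.
- **Per-patient mean:** make this the primary comparison, which is the quantity that the sample size powers.

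Whichever is chosen, report circuits per patient by arm.

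The change takes a sentence or two and needs no new data; R is already among the planned software. With clustering, confidence intervals will be wider than from a naive pooled analysis, and there is slightly more analysis work. The first-filter option sets aside information from later circuits.

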### Assignment of interventions: allocation

#### Sequence generation

A statistician who was not involved in the trial used the SPSS 24.0 software to generate a random allocation sequence. Based on the random allocation results, the participants were randomly assigned to the nafamostat mesylate group or the heparin group in a 1:1 ratio.

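### The unadjusted filter-life comparison is valid but forgoes precision: adjusted models are only sensitivity analyses with an open-ended covariate set, although candidate covariates are already collected at baseline

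*Protocol article*

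**What the plan says.** All references are to the protocol article.

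- **Main comparison.** The section on statistical methods for primary and secondary outcomes gives a t-test or a Mann–Whitney U test for continuous variables, depending on a normality test. For filter life it adds Kaplan–Meier curves with a log-rank test. None of these uses a covariate.
- **Role of adjustment.** The same section says that "multivariable linear regression and Cox proportional hazards models were used as sensitivity analyses". The reason given is "To control for potential confounders (e.g., disease severity scores". The section on additional analyses again plans adjusted regression against confounding, with no covariate list.
- **What is collected.** SOFA and APACHE II are scored at enrolment (plans for assessment and collection of outcomes). The outcomes section lists "coagulation parameters(include aPTT, PT, fibrinogen, platelet count", and the footnotes to Table 1 give these a baseline value. Platelet count is also an eligibility criterion, so a value before randomisation must exist.
- **Allocation.** An independent statistician "used the SPSS 24.0 software to generate a random allocation sequence". The article mentions no stratification.
- **Sample size.** It rests on the "approximate formula for comparing the means of two independent samples", which is an unadjusted comparison.

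**The concern.** In a 1:1 randomised trial, baseline variables differ between arms only by chance, so confounder control is not the reason to adjust. The reasons are precision and correction of chance imbalance. Both argue for putting a few prognostic baseline values into the primary model. Treating adjustment as protection against confounding leads naturally to the plan's choice: an unadjusted main result, with adjusted models behind it as a check.

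Two things are at stake. First, the design has no spare power at its evaluable sample size, so even a modest gain is useful. Second, an open-ended covariate set used in two model types (linear and Cox) leaves several adjusted results possible, with nothing in the article to say which one counts. The endpoint depends partly on bedside decisions in an open-label trial, as the limitations section acknowledges, so one adjusted model fixed in advance would carry more weight.

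**Working it through.** **Inputs from the sample size section.** "Assuming a two-sided α level of 0.05 and a power (1–β) of 80"%; "A minimum clinically important difference of 4 h"; "we deliberately chose a relatively conservative value (σ = 8 h"); 63 evaluable and 70 recruited per arm after about 10% dropout. R², the share of the variance of filter life explained by the covariates, is not in the documents. I assume 0.01 to 0.25.

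**Step 1: the plan's own figure.** n per arm = 2 × (1.960 + 0.842)² × 8² / 4² = 62.8, rounded up to 63. Then 63 / 0.9 = 70. Both stated figures reproduce. At 63 per arm the normal approximation gives 80.1% power and the exact noncentral t gives 79.5% (64 per arm gives 80.1%). I use the exact value below.

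**Step 2: power with adjustment.** In a linear model of per-patient mean filter life, the residual SD is 8 × √(1 − R²). The noncentrality is 4 / (residual SD × √(2/63)). The 8 h is taken as the SD of the patient-level mean.

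| Assumed R² | Residual SD (h) | Power, 63 per arm |
|---|---|---|
| 0 (unadjusted) | 8.00 | 79.5% |
| 0.01 | 7.96 | 79.9% |
| 0.04 | 7.84 | 81.1% |
| 0.10 | 7.59 | 83.5% |
| 0.25 | 6.93 | 89.5% |

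As a sample-size equivalent, the formula in step 1 gives 61 per arm for 80% power at R² = 0.04 and 48 at R² = 0.25, against 63 unadjusted.

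**Step 3: what adjustment costs.** Two lost degrees of freedom out of 124 change power by about 0.01 percentage points. Chance imbalance in k covariates also inflates the variance by an expected factor of 1 + k/(N − k − 3). With k = 2 and N = 126 this is 1 + 2/121 = 1.0165. Two covariates with no predictive value would therefore take power from 79.5% to about 78.9%. Break-even is at (1 − R²) × 1.0165 = 1, or R² = 2/123 = 0.016. After this charge, the powers for R² of 0.01, 0.04, 0.10 and 0.25 become about 79.3%, 80.5%, 82.9% and 89.0%.

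**Step 4: which covariates are pre-treatment.** The Table 1 footnotes equate baseline with allocation and Day 1. The data collection section counts day 1 among the follow-up days after randomisation, and the abstract places day 1 after treatment. A Day 1 aPTT may therefore be drawn after anticoagulation has begun. Enrolment SOFA and the platelet count used for eligibility do not have this problem.

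**The case against.** The strongest reply is that nothing here is wrong. An unadjusted comparison of randomised arms is valid, agrees with the sample-size calculation, and is commonly paired with adjusted sensitivity analyses. The covariate list may sit in an analysis plan that is not shown. The gain is unproven: filter life has no baseline measurement, and no passage says how well SOFA or platelets predict it. Most of this stands, and it limits the point to one of efficiency. It does not remove the point, because the protocol itself fixes the secondary role of the adjusted models and the reason for them, and an analysis plan that follows it would inherit both.

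Four stronger readings are tempting and not supported:

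- **That precision is being given away free.** At R² of about 0.01 there is no net gain.
- **That the confounders are wholly unnamed.** Severity scores are given as an example; what is missing is a closed list.
- **That covariates will be picked from baseline tests.** The article does plan between-group tests of etiology, CT scores and intra-abdominal hypertension, but nowhere says they will select covariates.
- **That the power figures apply to every planned analysis.** They apply only to a linear model of a mean. They do not carry over to Mann–Whitney, log-rank or Cox, and in a Cox model adjustment changes the quantity estimated to a conditional hazard ratio.

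The lack of any stated stratification may likewise reflect condensation in the article and is not treated as a fault.

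**Conclusion.** The point holds as a recommended improvement. The primary comparison is sound and powered as planned, but it leaves unused baseline information that is already being collected, and the stated rationale for adjustment does not fit a randomised trial. For the linear model the benefit runs from nothing (R² of about 0.016 or less, after the cost of two covariates) to roughly ten percentage points of power at R² = 0.25. The expected worst case is a loss of about 0.6 points. This rests on three assumptions: the 4 h difference and 8 h SD hold for per-patient means, the relation to the covariates is roughly linear, and the covariates are measured before treatment. Where in the R² range this trial lies cannot be settled from the documents.

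**What to change.** 1. Make one model primary for the mean filter-life endpoint: linear regression of per-patient mean filter life on arm plus a short, fixed list of continuous pre-treatment covariates, for example enrolment SOFA and platelet count. Add aPTT only if the sample is confirmed to precede the study anticoagulant.
2. Keep the unadjusted comparison as supportive.
3. If the time-to-event analysis is adjusted, use the same list in the Cox model and state that it estimates a conditional hazard ratio.
4. Replace the confounding rationale with precision and chance imbalance, in both places where it appears.
5. State that covariates are not chosen from the data, including from baseline significance tests.
6. Define baseline as a time before the first dose of anticoagulant, and reconcile the differing uses of day 1.

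The cost is analysis wording, plus confirmation of when baseline samples are taken. No extra patients or measurements are needed, and the sample size can stay as it is.

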#### Plans to promote participant retention and complete follow-up

This study will be conducted in the ICU, and most outcomes will be assessed during hospitalization. Therefore, the risk of loss to follow-up is expected to be very low. Monitoring during CRRT and standard clinical and laboratory assessments are part of routine intensive care unit care. If the patient is transferred to general ward before all planned observations are completed, the required result data will be obtained from the electronic medical record. If the patient has been discharged, the researchers will contact the participant or their family by phone. Reasons for withdrawal or incomplete follow-up will be recorded.

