#### Methods in analysis to handle protocol non-adherence and any statistical methods to handle missing data

Because of the prospective design and short follow-up period of this trial, the occurrence of missing data in this study will be rare. Protocol deviations will be incorporated within an intention-to-treat framework, supported by a per-protocol analysis, while missing data will be handled primarily with mixed-effects models and, when necessary, multiple imputation with sensitivity checks.

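### Repeated secondary outcomes: RM-ANOVA, change-from-baseline tests and mixed-effects models are all named, and the protocol does not say which result is the reported one

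*Protocol article*

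**What the plan says.** The section on statistical methods for primary and secondary outcomes covers the severity scores, pancreatic enzymes and inflammatory markers "measured on Day 1 (baseline), day 3, day 5, and day 7 after randomization". For these it states: "To evaluate time-dependent trends and group differences, a repeated-measures analysis of variance (RM-ANOVA) was applied", and the sentence goes on to limit this to variables with a normal distribution. It then adds "The assumption of sphericity was tested by" Mauchly's test, with the Greenhouse-Geisser correction if sphericity fails. Later in the same paragraph, between-arm differences in change from baseline are tested by t-test or Mann-Whitney U.

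The section on non-adherence and missing data says that "missing data will be handled primarily with mixed-effects models and, when necessary, multiple imputation with sensitivity checks". It names no outcomes and does not mention RM-ANOVA. The statistical methods section does not mention a mixed-effects model.

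On completeness, the missing-data section expects few missing values. The retention section foresees transfer to a general ward before all observations are complete, and says that then "the required result data will be obtained from the electronic medical record". The sample size section inflates recruitment with the words "Taking into account the approximately 10% dropout rate".

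**The concern.** Mauchly's test and the Greenhouse-Geisser correction identify the classical RM-ANOVA. It needs a complete row of four values per patient and leaves out anyone who lacks one. A mixed-effects model uses whatever values each patient has. Once a single value is missing, the two are different analyses on different sets of patients. The change-from-baseline tests are a third route through the same data, on yet another set of patients at each day.

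Two things are at stake. First, precision: RM-ANOVA discards measurements that were taken. Second, the patients left out are unlikely to be a random sample. Some will have died and others will have improved and left the ICU, so the arms compared are no longer quite those that were randomised. The Discussion relies on these outcomes to show an anti-inflammatory effect of nafamostat mesylate beyond anticoagulation. A reader of the results should therefore be able to tell which of the three analyses was meant to carry that conclusion.

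**Working it through.** **The plan's own figure.** The point disputes no stated number. The sample size reproduces: n = 2(1.96 + 0.8416)² × 8² / 4² = 62.8, so 63 per arm, and 63 / 0.9 = 70. It concerns filter life and is untouched here.

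**Inputs.** 70 patients per arm (sample size section); four measurements, of which three are post-baseline (statistical methods section). The protocol gives no missingness rate for days 3, 5 and 7. The rates p below are assumptions, with baseline taken as complete.

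**Patients kept, missingness independent across visits.** RM-ANOVA keeps 70(1 − p)³. A mixed model with baseline as covariate keeps anyone with at least one post-baseline value, 70(1 − p³). The values present at any one visit number 70(1 − p).

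| p per visit | RM-ANOVA, per arm | Mixed model, per arm | Values present at a visit | Share of those discarded by RM-ANOVA |
|---|---|---|---|---|
| 5% | 70 × 0.857 = 60 | 69.99 | 66.5 | 9.8% |
| 10% | 70 × 0.729 = 51 | 69.93 | 63 | 19.0% |
| 15% | 70 × 0.614 = 43 | 69.76 | 59.5 | 27.8% |

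The discarded share is 1 − (1 − p)². For a difference at one visit, the standard error from complete cases, relative to that from all values present at the visit, is √[(1 − p)/(1 − p)³] = 1/(1 − p). That is 1.05, 1.11 and 1.18, before any gain that the mixed model draws from the correlation between visits.

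**Patients kept, monotone loss.** If a fraction d is lost for good by day 7, RM-ANOVA keeps 140(1 − d) of the 140 patients: 133, 126, 112, 98 and 84 for d = 5, 10, 20, 30 and 40%.

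**Bias.** Independent missingness costs precision but does not bias the estimate. Bias needs loss that is related to the outcome.

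- Simulation with assumed inputs: 70 per arm, unit SD, correlation 0.6 between visits, true arm difference −0.40 SD, and loss after day 3 or day 5 more likely with a high last value in both arms. With 80–86% completers, complete cases gave −0.38 and the likelihood-based estimate −0.41. With 68–76% completers they gave −0.36 and −0.40.
- A second set of runs on SOFA-like data: 70 per arm, true effect −1.5. With loss at both extremes and 75% complete, complete cases gave −1.47 (standard error 0.47) and the likelihood-based estimate −1.51 (0.46). With loss at opposite extremes in the two arms, complete cases gave −1.41, or −1.58 when the arms were swapped.

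In these settings the bias is small beside the standard error, and it can go either way. Loss driven by the last observed value is also the condition under which likelihood-based estimates perform well, so the simulations favour the mixed model by design.

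**The case against.** The strongest reply is that the two sections are sequential: one names the analysis, the other says what happens when values are missing, with mixed-effects models first and multiple imputation second. On that reading the plan already has its answer, and the model details can be left to an analysis plan that is not shown.

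Part of this stands. A reader might infer that the alternatives are undeclared, or that missing data were overlooked. They were not: a method is declared, with an order between mixed models and imputation. What is missing is the link. Neither section says that the mixed model replaces RM-ANOVA, or which of the two is reported. Since the article itself commits to both, this is more than detail left to a later document. That the mixed models are meant for these outcomes is an inference, but a strong one, because these are the main repeated patient-level data.

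Other stronger readings also fail:

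- **That RM-ANOVA breaks the plan's intention-to-treat commitment.** The text reads "Protocol deviations will be incorporated within an intention-to-treat framework". The clause concerns protocol deviations; missing values are dealt with separately.
- **That all repeated markers go through RM-ANOVA.** Only the normally distributed ones do. For the others, the section offers only the change-from-baseline comparisons.
- **That complete-case analysis necessarily pulls the effect towards zero.** The direction depends on who is lost from which arm.
- **That the 10% dropout allowance, or the background mortality of up to 40%, is a missingness rate for these visits.** The first is a sample-size allowance for filter life. The second refers to patients with persistent organ failure and is not a day-7 figure.
- **That values are lost on ward transfer.** The plan is to take them from the electronic record. Whether ward records hold every score item and cytokine is not stated.

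**Conclusion.** The point holds as a reconciliation of two sections and a better choice of method. For normally distributed repeated secondary outcomes, the protocol names an analysis that needs complete series unless data are imputed, a second set of tests on changes, and a different model for missing data, without saying which is reported.

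If 5–15% of values were missing independently at each post-baseline visit, RM-ANOVA would keep about 60 down to 43 of 70 patients per arm and discard about 10–28% of the values observed at each visit. Those rates are assumptions. If missing values prove as rare as the protocol expects, the loss is small: at 2% per visit, 140 × 0.98³ ≈ 132 of 140 patients remain. The bias is modest in the settings examined and has no fixed sign. The primary endpoint and the sample size are not affected. The change is worth making because it is cheap and settles the reported analysis before the data are seen.

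**What to change.** In the statistical methods section, replace RM-ANOVA, Mauchly's test and the Greenhouse-Geisser correction with one mixed model for repeated measures:

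- All randomised patients, with every available value at days 3, 5 and 7.
- Terms for baseline value, arm, day and arm-by-day, with an unstructured covariance matrix.
- Skewed markers log-transformed, so that the model does not depend on a normality test of the trial data.
- The arm difference at each day, with its confidence interval, as the reported result.

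Label the change-from-baseline t-tests and Mann-Whitney tests as supportive; otherwise they remain a competing analysis of the same data. In the missing-data section, refer to this model by name and keep multiple imputation as a sensitivity analysis.

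State how death before day 7 is treated. A mixed model on available values implicitly carries scores beyond death, so it does not settle this by itself. One option is a sensitivity analysis that ranks death as the worst outcome.

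The cost is wording and slightly more analysis work. No sample size, visit or data item changes, and both R and SPSS, which the protocol already names, can fit the model.
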